## Abstract

**Background:**

Trocar Site Incisional Hernia (TSIH) is the most common postoperative complication after laparoscopic surgery, with incidences exceeding 30% in high-risk patients. Despite advances in minimally invasive approaches, optimal preventive strategies remain uncertain, and evidence comparing closure or reinforcement techniques is limited. Prophylactic mesh use shows benefits in open surgery, but its role in laparoscopy requires further clarification.

**Objective:**

The PRESUME study evaluates whether prophylactic sublay mesh placement at the umbilical trocar site reduces TSIH incidence in patients undergoing laparoscopic cholecystectomy who present at least one established risk factor. Secondary objectives include assessing mesh-related complications and short- and long-term postoperative outcomes.

**Methods:**

This prospective, multicentre, randomised controlled trial provides Level I evidence. Eligible participants are adults scheduled for laparoscopic cholecystectomy with diabetes mellitus, BMI ≥30 kg/m^2^, age ≥65 years, or requiring umbilical incision enlargement. Patients will be randomised 1:1 to standard aponeurotic closure or intraperitoneal sublay mesh reinforcement (Ventralex™ ST). Follow-up visits are scheduled at 30 days, 6 months, 1 year—with ultrasound—and 2 years. The principal investigator will remain blinded during follow-up. The primary endpoint is TSIH incidence; secondary outcomes include surgical site events, postoperative pain, readmissions, and time to return to daily activities. Based on expected TSIH reduction from 35% to 10%, 42 patients per arm are required.

**Discussion:**

TSIH remains a significant postoperative issue with limited preventive evidence in laparoscopy. By assessing the efficacy and safety of prophylactic sublay mesh reinforcement, the PRESUME trial may support future recommendations and improve outcomes in high-risk patients.

## Introduction

An incisional hernia (IH) is defined as a defect in the abdominal wall at the site of a previous surgical incision, detectable through physical examination and/or imaging techniques [1]. In laparoscopic procedures, this entity is further classified as a Trocar Site Incisional Hernia (TSIH) or Port Site Hernia (PSH), depending on the terminology used.

Every year, around 1,000 incisional hernias are operated on in Spain. Despite significant advancements in anesthetic techniques, postoperative care, surgical methods, suture quality, and antibiotic prophylaxis, complications related to abdominal wall closure remain prevalent. These complications include hematomas, surgical site infections, eviscerations, and incisional hernias (IH). They result in hospital readmissions, increased healthcare resource utilization, and higher associated costs. These events negatively affect surgical outcomes and diminish patients’ quality of life.

Numerous studies have advocated for the use of prophylactic mesh during abdominal wall closure in open surgery, demonstrating a reduction in the incidence of postoperative hernias [2]. However, the widespread adoption of laparoscopic surgery since its introduction in 1987 has not eliminated such complications. On the contrary, TSIH/PSH remains the most frequent postoperative complication associated with minimally invasive techniques [3, 4].

It is now recognized that a lack of medium- and long-term follow-up contributes to underdiagnosis of TSIH, particularly since many patients remain asymptomatic or do not seek medical care. Accurate diagnosis often requires a combination of thorough physical examination and imaging modalities such as ultrasound or CT scanning. Recent studies report a surprisingly high incidence of TSIH, ranging from 25.9% in procedures like laparoscopic cholecystectomy to 37.1% in more complex interventions such as laparoscopic colorectal surgery [4–6].

Established risk factors for TSIH include a body mass index (BMI) ≥30 kg/m^2^, age ≥65 years, and enlargement of the umbilical trocar incision [5].

While not all cases of TSIH are diagnosed—largely due to inadequate follow-up—and not all require surgical intervention, the growing use of laparoscopic techniques has rendered trocar site hernias a significant healthcare concern. The most promising strategy to address this issue lies in preventive measures. Although consensus exists among experts on the importance of prevention, relatively few studies have specifically investigated prophylactic strategies. Previous research by our group examined the use of a prophylactic supra-aponeurotic mesh but failed to demonstrate sufficient efficacy in preventing TSIH(7).

### Main and Secondary Hypothesis

The aim of the PRESUME study is to evaluate the effectiveness of a prophylactic sublay mesh in reducing the incidence of TSIH in patients at increased risk. We hypothesize that placement of a prophylactic sublay mesh at the umbilical trocar site in patients undergoing laparoscopic cholecystectomy with one or more established risk factors will significantly reduce the incidence of TSIH compared to standard closure without mesh reinforcement.

Secondary objectives include:Quantifying the incidence of complications at the umbilical trocar siteAssessing the impact of routine prophylactic mesh placement on the incidence of TSIH in high-risk patientsEvaluating both short-term and long-term complications associated with the use of prophylactic mesh

## Methods and Design

### Ethics and Permissions

This study will be conducted in accordance with the ethical principles outlined in the Declaration of Helsinki and will comply with current data protection regulations, including the European Union’s General Data Protection Regulation (EU GDPR 2016/679). Informed consent will be obtained from all participants prior to enrollment, and all personal data will be securely managed and anonymized.

The institutional review boards of the two participating hospitals have approved this randomized controlled trial. The study protocol has been reviewed and approved by the ethics committee of the coordinating center, Parc Sanitari Hospital Sant Joan de Déu (CEIC approval number: [PS-12-22]) in June 2022, as well as by the institutional review board of the other participating center, Consorci Sanitari del Maresme (CEIC approval number: [31/23]) on May 2023.

### Patient Evaluation and Selection (Inclusion/Exclusion Criteria)

Patient recruitment will be conducted by the surgeon during routine preoperative consultations. The study will be offered to adult patients (aged ≥18 years) scheduled to undergo laparoscopic cholecystectomy who fulfil at least one of the inclusion criteria. The inclusion criteria comprise the following risk factors for trocar incisional hernia: diabetes mellitus, body mass index (BMI) ≥30 kg/m^2^, age ≥65 years, or intraoperative enlargement of the umbilical trocar incision (Figure 1).

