**FIGURE 1 F1:**
[figure not shown]
Flow chart.

Exclusion criteria include a history of umbilical hernia, prior laparotomy at the umbilical site, or the need for intraoperative conversion to open surgery.

Eligible candidates will receive both verbal and written information regarding the study, including an informed consent document. Participation will be entirely voluntary, with no incentives or coercion involved.

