### Randomization Procedure

Participants will be randomized immediately prior to surgery using a computer-generated randomization sequence, in accordance with CONSORT guidelines. Patients will be assigned to one of two groups:Control Group: Umbilical trocar site closure will be performed using the standard technique (continuous suture).Study Group: A reinforcing intraperitoneal mesh will be placed at the umbilical trocar site following continuous suturing.

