### Intervention

The umbilical port will be inserted using the Hasson technique, which requires a transverse incision of aponeurosis. The placement and insertion of additional trocars will be at the discretion of the operating surgeon. The laparoscopic cholecystectomy will be performed in a standard fashion, with the specimen extracted via the umbilical trocar site using an endoscopic retrieval bag. If necessary, the incision may be extended, and the final length of the aponeurotic incision will be recorded.

In the control group, aponeurotic closure will be performed using a continuous suture with 0 polydioxanone. In the study group, a reinforcing mesh will be placed in an intraperitoneal sublay position, and the same continuous 0 polydioxanone suture will be used for mesh fixation. A 4.3 cm composite mesh (Ventralex™ ST Hernia Patch, Bard Davol, New Jersey, USA) will be used in the study group. This mesh consists of an anterior layer of polypropylene monofilament and a posterior absorbable hydrogel barrier, which permits safe contact with the peritoneal cavity. The intraperitoneal sublay position allows for a reduction in surgical time required for mesh placement.

Both groups will receive a single dose of 2 g of cefazolin preoperatively. Local anesthesia will be administered at all trocar insertion sites.

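### Intraoperative enlargement of the umbilical incision is a stand-alone inclusion criterion, but it cannot be known when patients are recruited, consented or randomised

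*Protocol article*

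**What the plan says.** All references are to the protocol article.

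- **Who is eligible.** Patient Evaluation and Selection offers the study to adults "scheduled to undergo laparoscopic cholecystectomy who fulfil at least one of the inclusion criteria". The last of the four listed factors is "or intraoperative enlargement of the umbilical trocar incision". The Abstract (Methods) repeats it as its own route into the trial: "or requiring umbilical incision enlargement".
- **When patients are recruited.** The same section states: "Patient recruitment will be conducted by the surgeon during routine preoperative consultations".
- **When consent is taken.** Ethics and Permissions states: "Informed consent will be obtained from all participants prior to enrollment".
- **When allocation is made.** Randomization Procedure states: "Participants will be randomized immediately prior to surgery using a computer-generated randomization sequence".
- **When enlargement happens.** Intervention mentions it together with removal of the specimen through the umbilical port: "If necessary, the incision may be extended, and the final length of the aponeurotic incision will be recorded". Data Collection and Analysis lists it among the intraoperative factors.
- **A related exclusion.** The exclusion criteria, printed after Figure 1, end with "or the need for intraoperative conversion to open surgery". This too is known only once surgery is under way.

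**The concern.** An inclusion criterion has to be checkable when a patient enters the trial, and at the latest at randomisation. This one is not. The eligibility and allocation rules are each stated explicitly, and they cannot all be followed for a patient whose only risk factor is enlargement.

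The stake depends on how sites resolve the conflict. If they follow the recruitment rule, one of the four published routes into the trial is empty. The comparison is sound, but the population is misdescribed. If they try to honour the fourth criterion, they must randomise patients who meet no criterion and decide afterwards whether those patients count. Membership of the analysed groups would then depend on a decision in theatre made after allocation. The Blinding section covers the principal investigator during follow-up. The article does not say that the operating surgeon is unaware of the allocation when deciding whether to extend the incision. With two participating hospitals, the two practices could also coexist in one trial.

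**Working it through.** **1. The sequence.** For a patient without diabetes, with BMI below 30 kg/m² and aged under 65:

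| Step | Timing in the article | Is a criterion met? |
|---|---|---|
| Offer of the study | Preoperative consultation | No |
| Consent | Before enrolment | No |
| Randomisation | Immediately before surgery | No |
| Possible enlargement | During the operation | Only now, and only if enlarged |

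For a patient who already has a preoperative factor, enlargement adds nothing to eligibility. For everyone else it comes too late. As sequenced, the criterion admits nobody.

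**2. Literal reading.** Patients with enlargement as their only factor are absent. Patients enrolled for diabetes, BMI or age may still have the incision extended, and the extension is recorded. The trial can therefore contain enlarged incisions, and no bias arises.

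**3. Alternative practice (not stated in the article).** Suppose patients without a factor are randomised and kept only if enlarged. With enlargement rate q, each retained patient requires 1/q randomised. The article gives no rate, so 10% to 40% is assumed. To retain 10 such patients:

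- q = 0.10: randomise 10/0.10 = 100, discard 90
- q = 0.20: randomise 10/0.20 = 50, discard 40
- q = 0.40: randomise 10/0.40 = 25, discard 15

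The whole trial is 2 × 42 = 84 patients.

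**4. Possible bias at the stated size.** The 42 per group is taken as stated in Sample Size Calculation. The other inputs are assumptions: 35 preoperatively eligible patients per arm with hernia risk 30%, M = 42 − 35 = 7 patients per arm without a factor, risk 50% if enlarged, and an enlargement (retention) rate that differs by arm. With no mesh effect, the rate in an arm is

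(35 × 0.30 + M × q × 0.50) / (35 + M × q).

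- q = 0.20: (10.5 + 0.70)/36.40 = 30.8%. q = 0.35: (10.5 + 1.225)/37.45 = 31.3%. Gap about 0.5 points.
- q = 0.15: (10.5 + 0.525)/36.05 = 30.6%. q = 0.40: (10.5 + 1.40)/37.80 = 31.5%. Gap about 0.9 points.

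Replacing the assumed 30% by the article's own figure of about 35% for high-risk patients (35 × 0.35 = 12.25) narrows the gaps:

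- q = 0.20 and 0.35: 12.95/36.40 = 35.6% and 13.475/37.45 = 36.0%. Gap about 0.4 points.
- q = 0.15 and 0.40: 12.775/36.05 = 35.4% and 13.65/37.80 = 36.1%. Gap about 0.7 points.

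The planned difference is 35% − 10% = 25 points. The gap grows with M, so these figures are tied to the assumed 7. Nothing in the article says which arm would have more enlargements, so the direction is open.

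**The case against.** The strongest reply is that the literal text leads to the harmless outcome: patients without a preoperative factor are simply not offered the study, and one phrase is redundant. It can be added that the article is a condensed document and that Figure 1, cited at the criteria, is not shown and may set out an in-theatre sequence. The first part stands as to bias. It does not remove the misdescribed population, nor the invitation to handle the criterion differently. If Figure 1 gave another order, it would conflict with Randomization Procedure, and the two would still have to be reconciled. Reading the criterion as anticipated enlargement might fit the Abstract's wording, but not the word intraoperative in the criteria or the classification in Data Collection and Analysis.

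A reader might also infer stronger points, which the documents do not support:

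- **That the trial discards randomised patients.** No passage says so. It is one way of trying to apply the criterion.
- **That no enlarged incisions would be studied, or that a conclusion is promised for such patients.** Only the enlargement-only patients would be missing. The hypothesis concerns patients with one or more risk factors, and no separate conclusion is stated for enlargement.
- **That the bias is several points.** With 25 to 50 no-factor patients added to 35 per arm, the same formula gives about 1.5 to 2.2 points (q 0.20 against 0.35) and 2.5 to 3.7 points (q 0.15 against 0.40). That means randomising 60 to 85 per arm, against a stated 42.

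**Conclusion.** The point holds as a contradiction between the stated eligibility rule and the stated times of recruitment, consent and randomisation. It rests on the article's text and needs no outside figure. Read literally, it is a defect in the definition of the population, without bias. If sites instead settle eligibility after allocation, the comparison is no longer between the randomised groups. The size and direction of the resulting bias cannot be determined from the article. The illustration of 0.5 to 0.9 points suggests that it is likely small at 42 per arm, but every rate and the 35/7 split behind it are assumed. The reason to act is structural: the rules cannot all be followed, and patients removed after allocation cannot be reliably restored at analysis.

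**What to change.** Make the Abstract (Methods), Patient Evaluation and Selection, and Randomization Procedure agree by choosing one of two routes.

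- **(a) Allocate in theatre.** Take consent before surgery from every patient scheduled for laparoscopic cholecystectomy who has no preoperative exclusion. Confirm eligibility and release the allocation after specimen extraction and immediately before umbilical closure. Enlargement is then known, and the exclusion for conversion to open surgery is also settled before allocation.
- **(b) Keep allocation before surgery.** Define the population by diabetes, BMI and age only, and keep enlargement as a recorded intraoperative variable, as Data Collection and Analysis already does. Analyse every randomised patient as randomised, with no removal for enlargement status or for conversion. The conversion exclusion must be reworded to match.

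Both need a protocol amendment. Route (a) adds an in-theatre allocation step, for example a REDCap module or sealed envelopes, and the consent of some patients who are never randomised. Route (b) costs only a slightly narrower stated population.

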**FIGURE 1 F1:**
[figure not shown]
Flow chart.

Exclusion criteria include a history of umbilical hernia, prior laparotomy at the umbilical site, or the need for intraoperative conversion to open surgery.

Eligible candidates will receive both verbal and written information regarding the study, including an informed consent document. Participation will be entirely voluntary, with no incentives or coercion involved.

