### Sample Size Calculation

The primary outcome for the sample size calculation is the incidence of umbilical trocar site hernia. Based on published data, the expected incidence of umbilical trocar site hernia in high-risk patients is approximately 35%. The study hypothesises that prophylactic mesh placement will reduce the incidence to 10%; therefore, we assume a 25% reduction.

Assuming a 25% reduction in umbilical trocar site hernia, a two-sided alpha risk of 0.05 and a power of 80% (β < 0.2), and accounting for a 10% dropout or loss to follow-up, the random sample size is 42 patients per group to detect a statistically significant difference between the intervention and control groups.

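### Conversion to open surgery is an exclusion criterion, but patients are randomised before surgery, so the criterion can only act after the arm has been assigned

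*Protocol article*

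**What the plan says.** In the protocol article, Patient Evaluation and Selection, the exclusion criteria (placed just after the Figure 1 caption) end with "the need for intraoperative conversion to open surgery". Under Randomization Procedure, "Participants will be randomized immediately prior to surgery".

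The Intervention section describes one operation for both arms up to closure of the umbilical site. There the control arm gets a continuous suture and the study arm gets an intraperitoneal mesh as well. The Blinding section masks the principal investigator during follow-up and says nothing about what the operating team knows before closure.

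Data Collection and Analysis lists conversion among the recorded intraoperative factors. Sample Size Calculation gives the target as "the random sample size is 42 patients per group", "accounting for a 10% dropout or loss to follow-up". The article does not say whether converted patients are replaced, followed or analysed.

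**The concern.** An eligibility criterion should be settled before the arm is assigned. This one cannot be, because the event it names happens during an operation that starts after randomisation. Anyone who meets it has already been allocated, and removing that patient means the groups compared are no longer the groups that were randomised.

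Conversion is a decision made in theatre. If the team knows the arm by then, that knowledge could influence the decision or how it is recorded. Converted patients are also likely to be the harder cases, so those removed need not have average hernia or wound risk. With 42 patients per arm, a few removals that are uneven between arms could shift the estimate. The trial presents itself as Level I randomised evidence, which depends on keeping the randomised comparison intact.

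**Working it through.** **Order of events**

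1. Eligibility check and consent at the preoperative consultation (Patient Evaluation and Selection).
2. Allocation, immediately before surgery (Randomization Procedure).
3. Operation, identical by arm until closure (Intervention). Conversion, if needed, is decided here.
4. Umbilical closure, with or without mesh. This is the first point at which the arms differ.

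The exclusion is triggered at step 3 and the arm is fixed at step 2. No reading of the two sections lets the criterion act before allocation. Moving step 2 to just before step 4 removes the conflict without changing either closure technique.

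**How many patients.** The documents give no conversion rate; 1% to 10% is an assumption. With 2 × 42 = 84 randomised: 84 × 0.01 = 0.8, 84 × 0.05 = 4.2, 84 × 0.10 = 8.4.

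**Effect on power**

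Inputs from Sample Size Calculation: control rate 0.35 ("the expected incidence of umbilical trocar site hernia in high-risk patients is approximately 35"%), mesh rate 0.10 ("prophylactic mesh placement will reduce the incidence to 10"%), and "a two-sided alpha risk of 0.05 and a power of 80% (β < 0.2"). The allocation ratio is 1:1 (Abstract, Methods).

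The plan's own figure first, using the pooled two-proportion formula:

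n = [z(0.975)·√(2·p̄·(1−p̄)) + z(0.80)·√(p1(1−p1) + p2(1−p2))]² / (p1−p2)², with p̄ = 0.225.

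- First term: 1.960 × √0.34875 = 1.1575.
- Second term: 0.8416 × √0.3175 = 0.4742.
- n = (1.6317)² / 0.0625 = 42.6, so 43 per arm before losses, and 43/0.9 = 47.8, so 48 after a 10% loss.
- The unpooled form gives (1.960 + 0.8416)² × 0.3175 / 0.0625 = 39.9, so 40 before losses, and 40/0.9 = 44.4, so 45 after.

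The stated 42 is therefore close to the loss-free size and does not reproduce as a figure that includes 10% loss. That is a separate sample-size matter and is not used as evidence for this point; it only sets the baseline for the power figures below.

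Power = Φ{[0.25·√n − 1.1575] / 0.5635}, where n is the number evaluable per arm:

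| Assumed conversion rate | Evaluable per arm | Power |
|---|---|---|
| none removed | 42 × 0.9 = 37.8 | 75.0% |
| 1% | 37.8 × 0.99 = 37.4 | 74.5% |
| 3% | 37.8 × 0.97 = 36.7 | 73.6% |
| 5% | 37.8 × 0.95 = 35.9 | 72.7% |
| 10% | 37.8 × 0.90 = 34.0 | 70.3% |

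The table treats conversions as additional to the 10% loss. If the 10% already includes them, the first row applies. The cost attributable to conversion is thus between nothing and 75.0 − 70.3 = 4.7 percentage points over the assumed range, and 0.5 points at 1%.

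**Bias.** This cannot be computed. It depends on the conversion rate by arm and the hernia risk of converted patients, and neither is given.

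**The case against.** The strongest defence is that mesh cannot cause conversion: the arms are treated alike until closure, and conversion comes earlier. If the arm is not known before closure, exclusions should balance on average and the cost is to generalisability, not validity. That is right as far as it goes, but it relies on a masking step that the article does not describe.

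It can also be said that no analysis set is stated, that the flow chart and any SAP are not shown, and that handling of converted patients may be settled there. This stands in part. Removal from the analysis is inferred from the exclusion label and is not stated outright. The order of allocation and exclusion, however, is stated in the article.

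Three stronger readings are tempting, and the documents do not support them.

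- **A couple of exclusions would reverse the trial's result.** An example can be built: 15/42 against 8/42 gives p = 0.087 (Fisher 0.141), and removing two mesh-arm patients with hernias gives 15/42 against 6/40, p = 0.032 (Fisher 0.043). It is a worst case. One removal with a hernia per arm gives 14/41 against 7/41, p = 0.077. Two mesh removals with one hernia give 15/42 against 7/40, p = 0.063. Two without a hernia give 15/42 against 8/40, p = 0.113. Even the chosen case gives p = 0.058 with a continuity correction. If two conversions fall at random by arm and each patient has the planned 35% risk, the chance that both are in the mesh arm and both herniate is 0.25 × 0.35² ≈ 3%.
- **Listing conversion as a study variable contradicts excluding it.** Conversion has to be recorded in order to apply and report the exclusion, so the two are compatible.
- **Conversions necessarily come on top of the 10% allowance.** The word dropout could cover them; the text does not say.

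**Conclusion.** The point holds as a design fault in the timing of one criterion. As written, exclusion for conversion can only operate after randomisation, and nothing described prevents it from operating differently by arm.

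Its size is limited and partly unknown. Neither the direction nor the magnitude of bias can be derived from the documents. The power cost is small if conversion is rare, and reaches 4.7 points only at an assumed 10% conversion rate counted in addition to the full 10% loss. The conclusion rests on two things: that exclusion means what it normally means, so that converted patients leave the comparison, and that the arm may be known to the operating team before closure. It does not show that bias will occur. It should be corrected because the remedy is simple and protects the randomised comparison.

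**What to change.** **Preferred.** Amend Randomization Procedure so that the allocation is released during the operation, immediately before umbilical closure and after conversion has been ruled out. Conversion then becomes a true pre-randomisation exclusion and needs no allowance in the sample size. The cost is a change in theatre logistics: the allocation must be obtainable during the case. The same change would place intraoperative enlargement of the umbilical incision, an inclusion criterion that is also unknown before surgery, ahead of allocation.

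**If allocation must stay before surgery:**

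- remove conversion from the exclusion criteria;
- keep all randomised patients in their allocated arm for the primary comparison;
- prespecify how the primary endpoint is determined when a laparotomy involves the umbilical site, since a trocar-site hernia may then not be assessable as defined;
- report conversions by arm, using the variable already collected;
- show the analysis without converted patients as a sensitivity analysis only.

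This alternative costs more than a change of wording because the endpoint rule has to be written. It may also dilute the estimated effect slightly if converted patients in the study arm do not receive the allocated closure.
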